#### Goal 2—To Quantitatively Test the Effectiveness of This Intervention in Improving the Emotional Well-Being of Older Adults With ADRD

The objectives are to (1) provide a 10-session intervention with reminiscence and DST to older adults by trained young adult volunteers and (2) test whether older adults report significant changes in affect or resilience after the intervention. Hypotheses include the following: (1) older participants in the intervention group will have high positive affect (PA) and low negative affect (NA) in the middle of and after the intervention compared with their pretest scores and compared with those in control group and (2) older participants in the intervention group will have high resilience scores in the middle of and after the intervention compared with their pretest scores and compared with those in control group.

#### Goal 3—To Quantitatively Test Attitudes Toward Aging Among the Young Adult Volunteers

The objectives are to (1) offer opportunities for trained young adult volunteers to engage with older adults in the 10-session intervention and (2) test changes in their attitudes toward aging after the intervention using surveys. Hypotheses include the following: (1) young adult volunteers in the intervention group will have more positive attitudes toward aging after the intervention compared with that before the intervention and (2) young adult volunteers in the intervention group will have more positive attitude toward aging after the intervention compared with those in the control group.

#### Goal 4—To Quantitatively Test Knowledge and Awareness About ADRD Disease Among the Young Adult Volunteers

The objectives are to (1) offer a 3-hour training to the young adult volunteers before the intervention starts, which covers the biological aspects of ADRD and how to communicate and connect interpersonally to people with ADRD, and (2) test changes in their reported knowledge and awareness about ADRD using surveys. Hypotheses include the following: (1) young adult volunteers in the intervention group will report more knowledge and awareness about ADRD disease after the intervention compared with their pretest scores and (2) young adult volunteers in the intervention group will report more knowledge and awareness about ADRD disease compared with those in the control group after the intervention.

#### Goal 5—To Qualitatively Evaluate the Usefulness of This Intervention From the Perspectives of the Dyads

The objectives are to (1) explore and interpret the statistical results obtained in goals 1 and 2 through individual interviews with older adults who report the greatest and least changes in well-being; (2) explore and interpret the statistical results obtained in goals 3 and 4 through individual interviews with young adult volunteers who report the greatest and least changes in attitudes toward aging; and (3) examine dyad participants’ perceptions about the intervention in terms of its quality, benefits, and usefulness.

## Methods

### Study Design

The proposed project will conduct a randomized controlled trial to assess the effects of the intergenerational reminiscence approach with DST on the social and emotional well-being of older adults with ADRD. An explanatory sequential mixed methods design [39] will be used, which first involves collecting quantitative data and analyzing the data to identify subsamples of participants who report the greatest and least changes and then conducting qualitative interview with these subsamples. Half (46/92, 50%) of the dyad sample will receive the reminiscence DST intervention, and the other half (46/92, 50%) of the sample will receive a regular social visit from young adult volunteers without the intervention. Dyads will be randomly assigned to either the intervention or control group after baseline screening of all participants and, subsequently, randomly matched within each group. To further prevent selection bias, statistical techniques such as covariate-adjusted linear mixed models will be used to adjust for covariate imbalance during data analysis.

A total of 92 dyads are required to test the effectiveness of the intervention in this proposed study (refer to power analysis in the *Sample and Recruitment Plan* section). We will recruit participants on a rolling basis until we recruit 92 dyads. At least one-fourth (23/92, 25%) of the total sample of older adults and young adult volunteers will be recruited before they are randomly matched. Upon signing the consent form, participants will be given the chance to engage in the study. They will be provided with guidance throughout the informed consent process and will subsequently undergo a baseline survey in which all measures will be collected blind to group conditions.

The first group will receive the intervention (X), which includes reminiscence and DST components provided by the young adult volunteers, whereas the second group will serve as the sham control group, which will include social visits calls by the young adult volunteers and an unstructured, nondigital recording (eg, scrapbook or journal) of the social visits. To account for the potential influence of attention and social interactions stemming from the intervention, the control activity is intentionally designed to offer comparable social contacts. This ensures that any observed improvements in participants cannot solely be attributed to the intervention itself. The features of the intervention and sham protocols are the same, except that participants in the intervention group will participate in structured reminiscence and DST, whereas those assigned to the control group will be facilitated to do otherwise. Similar to the study by Lai et al [40], the sham protocol will include talking about overall issues related to wellness in later life (eg, diet and health, social activities, and family relationships) and creating a wellness scrapbook or journal.

As shown in Figure 1, data will be collected at baseline before the intervention, in the middle of the intervention, at the end of the intervention, and at 3 months after the intervention. The design of this study is depicted in scientific notation.

**Figure 1 figure1:**

Data collection overview. G1: first group; G2: second group; O1: before the intervention; O2: middle of the intervention; O3: end of the intervention; O4: 3 months after the intervention; X: intervention.

### Sampling and Recruitment Plan

Power analyses performed using G*Power 3.1.9 indicated that a total of 92 dyads (or 184 participants) are required to address our study objectives using a linear mixed model. This sample size estimate was based on a small effect size *(f*=0.22), a significance level of α=.05, β of .20, anticipated *r* over time of 0.30, and 5% attrition rate based on the findings of Chung [25], for 2-tailed tests.

Participants in this study will be community-dwelling older adults and undergraduate and graduate students (ie, young adult volunteers) enrolled at UTA. The eligibility criteria of the older adult participants include individuals who (1) are aged ≥65 years; (2) have cognitive impairment measured by the Ascertain Dementia 8 (AD8) [41]; (3) have decisional capacity as measured by the University of California, San Diego Brief Assessment of Capacity to Consent (UBACC) [42]; (4) are not participating in any other research protocol currently; and (5) can speak and understand English. The exclusion criteria for older adults are (1) participating in another trial, (2) having health issues that prevent them from participating in the study for 3 months, and (3) inability to commit to being available for the full 10 weeks of the intervention.

The older adult participants will be recruited through Tarrant County Meals On Wheels (MOW), which is a partner agency of the Area Agency on Aging of Tarrant County. Eligibility criteria to enroll in Tarrant County MOW is that a person must be homebound and have no one to help them on a regular basis. The Area Agency on Aging is very committed to expanding services and supports to people with ADRD, as many MOW clients with ADRD are living alone in Tarrant County. Moreover, studies suggest the need for additional research in the area of loneliness among clients using MOW [43]. Participant recruitment will begin with case managers and other MOW staff using their client database system to search for clients with ADRD who meet the study criteria. Next, case managers will contact potential study participants and then ask for permission to share their telephone number with a member of the UTA research team. The principal investigators (PIs) and graduate research assistants (GRAs) will follow-up with all the potential participants provided by MOW.

The young adult volunteers will include undergraduate or graduate students from UTA. The inclusion criteria for the young adult volunteers are the following: (1) aged 18 to 30 years, (2) currently enrolled as a student at UTA, and (3) can commit to be available for the full 10 weeks of the intervention. Young adult volunteers who have health issues or limited availability that prevent them from participating for the entire 10 weeks of the intervention will be excluded from the study. The study will be widely advertised across the UTA campus through avenues such as different student organizations, departmental social media accounts, departmental websites, and the offices of campus partners (eg, student health services, career services, campus recreation, and undergraduate honor program). Other recruitment efforts will include posting flyers across the campus, emailing student listserves, social media, advertising on television monitors located in buildings across campus, and classroom visits.

### Procedure

Before the intervention starts, the young adult volunteers in the intervention group and control group will be offered a mandatory separate group training through Microsoft Teams. Training for young adult volunteers in the intervention group will last 3 hours and be offered by LX, [name], [name], and [name]. Students will be provided with hard and electronic copies of the training materials. As part of the training, LX will cover an overview of the study and the intervention protocol, project timelines, responsibilities of the young adult volunteers, roles of the research personnel, and importance of human participants’ protection in the research activities. [name] will provide training related to ADRD, communication skills with older adults with ADRD, and how to deal with unexpected behavior or emotional symptoms of older adults during the intervention. [name] will cover how to communicate with older adults with ADRD. [name] will provide an overview of DST and details about DST techniques and demonstrate strategies for successful DST. Similarly, training for the young adult volunteers in the control group will be approximately 1 hour in duration and will cover human participants’ protection; study procedure (social visits); and explanation of the unstructured, nondigital record of the social visits. The trainings will be audio recorded and later analyzed for fidelity.

Subsequently, participants will participate in this telephone-based intervention. In this study, the young adult volunteers (in both the intervention and control groups) will talk with older adults through telephone calls each week for 10 weeks with the same process described in the following sections. Older adults in the intervention group will receive 10 sessions of life review with the trained young adult volunteers (1-1.5 hours each week for 10 weeks). During weeks 1 to 6, a life history interview will be conducted with different themes in each week: major turning points in life (W1), family history (W2), life or career accomplishments (W3), history of love and hate (W4), stress experiences (W5), and meaning and purpose of life (W6). Guidelines for conducting a life history interview will be prepared for the young adult volunteers based on the work of Watt and Cappeliez [44]. The implementation outline will encompass integrative and instrumental reminiscence techniques that aim to foster self-acceptance, conflict resolution, reconciliation, sense of purpose and self-value, recollection of effective coping strategies used in the past, and leveraging past experiences to address current challenges. After each session, the young adult volunteer will write a 1-page summary and reflect about the interview to help prepare for the subsequent DST in the later weeks. During weeks 7 to 10, the dyads will develop the DST together using tablets already owned by the UTA School of Social Work. The contents of sessions 7 to 10 will be structured as outline or script; plan and storyboard (W7); film and record (W8); evaluate, integrate, and finalize (W9); and publish or share (W10). It is acceptable if no filming or video aspect of the DST is conducted. Audio-based DST without video recording is still common, as it captures the voices that give life to the photos [27]. Photos obtained from the internet or the participants may be used as part of the DST to accompany the audio. For example, photos of the individual’s hometown, familiar places (ie, parks), familiar vacation locations (ie, monuments and historical markers), and so on, will help augment the voice recordings.

Older adults in the control group will have general social visit conversation with the young adult volunteers, and the content of weeks 1 to 6 will be based on general topics related to wellness in later life, instead of structured reminiscence guidelines. The topics of weekly social conversation are diet and health (W1), exercise or activity and health (W2), emotions and health (W3), religious or spiritual practices and health (W4), family or friend relationships and health (W5), and social activities or engagement and health (W6). For weeks 7 to 10, instead of DST, the young adult volunteer will work with the older adult to create an unstructured, nondigital record of the social visit related to wellness in later life (eg, wellness scrapbook or journal).

Every effort will be made to minimize risks by closely monitoring participants’ mood during weekly fidelity treatment checks. Weekly calls with the dyads in both the intervention and control groups will be conducted by the research team to closely monitor the participants’ mood and to serve as a fidelity check. These calls will include questions related to the study protocol (eg, topics covered, time spent, and challenges that occurred) and questions related to the well-being of participants (eg, How are you feeling? Do you need anything from the research team? and Are you experiencing any challenges?). If a study participant experiences emotional distress during the study, a clinical social worker and registered nurse practitioner, who are members of the research team, will offer consultation, and if necessary, they may refer study participants to additional services through the local Area Agency on Aging. Finally, individual retraining will be provided to the young adult volunteers in the case of problems with treatment fidelity.

To prevent contamination, the importance of confidentiality will be emphasized to participants in the intervention group at the beginning of the study. Participants (especially the young adult volunteers) in intervention group will be asked not to share the protocol with the participants in the control group for the duration of the study to minimize contamination. To further prevent contamination, the research team will check in with young adult participants in the intervention group 3 times (3 weeks, 6 weeks, and 9 weeks after the intervention starts) via telephone to ensure that no information has been shared with participants in the control group. Furthermore, young adult participants in the control group will also be asked 3 times during the study period whether they received any information related to the reminiscence and DST content, and this will be documented by the research team. In addition, substantial contamination can be tolerated within the usual individual randomized trial [45]. Finally, if contamination occurs, any documentation of hearing about or implementing reminiscence in the control group will be included as a covariate in the study analyses.

After the intervention, qualitative interviews with subsamples in the intervention group will be conducted. For the individuals in the highest 10% and lowest 10% of changes based on survey tests, we will conduct follow-up qualitative interviews to capture the details of their situations and present a more robust analysis, taking advantage of the strengths of both methods. The interview will last for 45 to 60 minutes and will be conducted by research teams through telephone calls.

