For quantitative data analyses, descriptive analyses will first be conducted to provide the overall means and frequencies of key outcome variables for both older and young participants in the intervention and control groups. Fisher exact tests, Pearson chi-square tests, and independent samples *t* tests (2-tailed) will be computed to test for group differences that may be attributable to participants, such as age, sex, education level, income, and health conditions. If the groups significantly differ on any of these variables, the variable will be incorporated into the following analyses as a covariate, thereby controlling for potential influences that the covariate may have on the dependent variables. Moreover, in the event that at the culmination of this study, our sample sizes are unequal in the treatment groups or our outcome data are nonnormal, we will follow through with appropriate statistical corrections where necessary. Covariate-adjusted linear mixed models for repeated measures will be performed to compare the intervention and control groups over time for the major outcomes of older adults and young adult volunteers. The covariate will be any significant variable yielded from the univariate analyses, and the dependent variable will be the scores before the intervention, in the middle of the intervention, at the end of the intervention, and at 3-month follow-up. In this study, 95% CIs will be computed for each adjusted mean difference. The study α will be set to .05, with no adjustments for multiple comparisons owing to the preliminary nature of this study and the increased risk of type-2 error as a result of α adjustment [70].

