### Data Management and Participants’ Safety

The research team will be the sole individuals with knowledge about and access to the names of both the older and young participants. Although certain demographic information, such as age, sex, and racial and ethnic background, may be recorded, the questionnaires will not contain any participant identifiers such as date of birth or address. The preintervention and postintervention questionnaires will also be devoid of participant identifiers. To ensure confidentiality, participant names will be deidentified, with each individual assigned a unique study identifier or number. All data files will be securely stored in encrypted, password-protected folders on laptops provided by UTA. These laptops will also have encryption in accordance with the guidelines set by the UTA Office of Information Technology. Participant privacy will be diligently safeguarded, and records containing names and other identifiable information will be stored separately from the interviews, using password-protected, encrypted files on UTA-issued laptops. The PI (LX) and the UTA institutional review board (IRB) will bear the responsibility of ensuring participant safety and the attainment of the study’s scientific objectives. The research team possesses previous experience in organizing and managing clinical trials, including implementing data safety monitoring measures for interventions.

All the older adults and young adult volunteers will provide informed consent before participating in the study. Potential participants will be informed that refusal to consent to the study or withdrawing from the study will have no effect on the services that they currently receive or might receive through UTA (ie, young adult volunteers) or through MOW or the Area Agency on Aging (ie, older adults). Participants who provide informed consent will be contacted for baseline measurement and then randomized to 1 of the 2 treatment groups. The protocol and consent forms will be approved by the UTA IRB before conducting any study procedures. Student members of the research team will receive training regarding procedures required to obtain informed consent.

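### If contamination occurs, entering it as a covariate makes the adjusted group effect a comparison with uncontaminated controls only, not the comparison as randomised

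*Protocol article*

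**What the plan says.** The rule is in the protocol article under Procedure. If contamination occurs, "any documentation of hearing about or implementing reminiscence in the control group will be included as a covariate in the study analyses". It is conditional on contamination, but it is not confined to a sensitivity analysis, and no main analysis without the covariate is stated.

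The information is collected during follow-up: "young adult participants in the control group will also be asked 3 times during the study period whether they received any information" about the reminiscence and digital storytelling content. Intervention volunteers are asked something different, namely whether they passed information on. Under Data Management and Participants' Safety, participants "will be contacted for baseline measurement and then randomized to 1 of the 2 treatment groups", so the contamination record always post-dates assignment.

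The sentence before the rule says that "substantial contamination can be tolerated within the usual individual randomized trial".

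Under Statistical Analysis, "Covariate-adjusted linear mixed models for repeated measures will be performed to compare the intervention and control groups over time", and "95% CIs will be computed for each adjusted mean difference". Baseline is one of the four scores modelled as the dependent variable.

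**The concern.** Covariate adjustment in a randomised trial is safe when the covariate is fixed before assignment. Study Design justifies adjustment as a remedy for covariate imbalance, which is a baseline argument. This covariate is of another kind: assignment determines who can have a non-zero value, and within the control arm it depends on what people did or heard afterwards.

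Putting it in the model does not remove the effect of contamination from the control arm. It removes the contaminated controls from the contrast, so in effect it is a per-protocol exclusion in one arm. If those controls differ in prognosis from the rest, the groups compared are no longer exchangeable and a difference can appear, or be hidden, without any treatment effect. Even if they do not differ, the estimate no longer answers what assignment to the intervention achieved.

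**Working it through.** **1. The plan's own figure.** The covariate rule rests on no stated number. The figure for the group-level comparison it would alter is the power of 0.71 with 64 dyads (Results; f = 0.22, α = .05, r = 0.30). With four measurements, λ = f²·N·m / (1 + (m − 1)r) = 0.0484 × 64 × 4 / 1.9 = 6.52. On 1 and 62 df this gives power 0.710, so the figure reproduces. For two equal groups, f = 0.22 is a difference of 2f = 0.44 SD, used below as a yardstick.

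**2. What the coefficient becomes.** Let A = 1 for intervention and C = 1 for a contaminated control, with C = 0 throughout the intervention arm. A model with A and C has three cells and three mean parameters, so it fits the cell means exactly:

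coefficient of A = mean(intervention) − mean(controls with C = 0).

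This needs no assumption about contamination. Simulated fits agreed with it in every case.

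**3. Size under no treatment effect.** The documents give neither the proportion contaminated (p) nor its link to prognosis, so both are assumed. Let an unmeasured factor correlate a with the tendency to be contaminated and b with the outcome (in SD units), and let z be the 1 − p quantile and φ the density of the standard normal. Then

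bias = a·b·φ(z) / (1 − p).

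The ratio φ(z)/(1 − p) is 0.195, 0.350 and 0.497 at p = 10%, 20% and 30%. Type I error is from simulation with one post-randomisation score and 46 per arm, the planned allocation ("Half (46/92, 50%) of the dyad sample will receive the reminiscence DST intervention").

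| a, b | p | Bias with C (SD) | Type I with C | Type I without C |
|---|---|---|---|---|
| 0, 0 | 10 / 20 / 30% | 0 / 0 / 0 | 5.2 / 4.7 / 4.8% | 5.0 / 4.6 / 4.9% |
| 0.5, 0.5 | 10 / 20 / 30% | 0.05 / 0.09 / 0.12 | 5.5 / 7.0 / 8.4% | 4.8 / 5.3 / 4.7% |
| 0.7, 0.7 | 10 / 20 / 30% | 0.10 / 0.17 / 0.24 | 7.2 / 12.7 / 19.0% | 4.9 / 4.7 / 5.1% |

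The sign of the bias reverses if contaminated controls have the worse prognosis. With 32 per arm (64 completing dyads, assumed split equally), type I error with C runs from 5.2% to 14.4% over the last two rows.

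**4. Size with a true effect.** Take 0.44 SD, p = 20%, and half the effect passed to contaminated controls. The randomised comparison estimates 0.44 × (1 − 0.2 × 0.5) = 0.40. With C the estimate is 0.44 if contamination is unrelated to prognosis. With links of 0.5 and 0.5 it is 0.44 + 0.09 = 0.53 if contaminated controls have the better prognosis, and 0.44 − 0.09 = 0.35 if the worse.

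**5. The planned repeated-measures model.** A random-intercept model with four visits and r = 0.30 was fitted to the better-prognosis case in step 4 (3,000 per arm, complete data).

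| Model | Group-by-time contrast, end vs baseline | Adjusted mean difference at end |
|---|---|---|
| No C | 0.378 | 0.405 |
| C as a time-constant main effect | 0.378 | 0.533 |
| C and C × time | 0.422 | 0.542 |

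A null version (4,000 per arm, p = 20%, links 0.5 and 0.5) was run to see when the group-by-time contrast moves:
- Stable prognostic factor, C × time: from 0.005 to −0.009, so no material shift.
- Prognostic factor acting only after baseline, C × time: from 0.002 to 0.099.
- C coded as time-varying and zero at baseline: from 0.005 to 0.059 with a stable factor, and from 0.002 to 0.086 with one acting only after baseline.

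**The case against.** The strongest reply is that the plan tests change over time. Statistical Analysis looks for a group-by-time interaction, and with a time-constant main-effect covariate and complete data that contrast is the same with and without C. This stands, and it defeats an inference a reader might draw, that the rule breaks the main analysis of every outcome. It does not clear the rule. The plan also reports adjusted mean differences, and Results names the between-group difference as a test; both shift. Contamination is asked about three times, so time-varying coding is a natural choice. Data were also not complete: 64 of 103 dyads completed the posttest.

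Second, the rule applies only if contamination occurs, and the protocol works to prevent it with confidentiality instructions, check-ins in both arms and weekly fidelity calls. This stands. With little contamination the term hardly matters.

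Third, the link to prognosis is conjecture. Exposure is asked of the students, the primary outcomes belong to the older adults, and the two are randomly matched within arm. A student's merely hearing about reminiscence has no evident route to the older adult's prognosis. The link is more plausible for implementing reminiscence and for the students' own outcomes. This limits what can be said about size. It does not restore the comparison as randomised.

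A reader might also infer that the covariate must favour the intervention. The documents do not support that; the direction depends on which controls are contaminated.

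**Conclusion.** The rule is wrong as written and should be changed. If it is triggered, the adjusted group effect and adjusted mean differences compare the intervention arm with uncontaminated controls. That follows from the coding alone, for an indicator that is zero throughout the intervention arm. The group-by-time contrast is safe only for a time-constant main effect with complete data.

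Size and direction are unknown. The range of about 0.05 to 0.24 SD in either direction, with type I error of 5.5% to 19%, holds for the group-level contrast under the assumed rates and links to prognosis. If contamination is unrelated to prognosis there is no bias under the null, but the quantity estimated still changes. The article's remark that substantial contamination can be tolerated in an individually randomised trial itself supports leaving the covariate out. A claim that the trial's main results are invalid would go beyond the documents, which report no contamination.

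**What to change.** Remove the contamination covariate from the main models. State that all dyads are analysed as randomised, with adjustment limited to variables measured before randomisation, and report the proportion of controls with documented contamination, separating hearing about reminiscence from implementing it.

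If an estimate adjusted for contamination, or of the effect without it, is wanted, present it as a labelled sensitivity analysis with its coding and assumptions stated. Using randomisation as an instrument is one option. It requires an exclusion restriction, which having merely heard about reminiscence may not satisfy.

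The cost is a change of wording and one optional analysis. Results says data cleaning and analysis were still under way, so no new data are needed. The downside is that the main estimate may be smaller if contamination occurred, because it then keeps the dilution that contamination causes.
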